## Abstract

**Background:**

Intestinal permeability is an important determinant in intensive care unit patients. Enteral nutrition is vital for nutritional supplementation in critically ill ICU patients. The amount of Enteral nutrition protein and its impact on intestinal barrier permeability and function are challenging issues. Zonulin is a protein that regulates intestinal epithelial cell tight junction permeability and has the potential to be used as a biomarker for assessing the integrity of the intestinal barrier. However, there are few data from studies on intestinal permeability and the effects of enteral feeding of protein on zonulin levels in critically ill patients. This study was conducted to investigate the effect of high-protein enteral nutrition on intestinal permeability in ICU patients.

**Methods:**

Participants were selected from 88 adult patients with critical illness aged 18-65 years who were admitted to the ICU of Hazrat Rasoul Akram Hospital in Tehran. In this randomized controlled clinical trial, patients will be allocated randomly into two groups of 44. The intervention group will receive high-protein (HP) enteral nutrition (1.6 g/kg/day), and the control group will receive conventional-protein (CP) enteral nutrition (1.2 g/kg/day) for 10 days. The primary outcome will be the change in serum Zonulin levels during the intervention period. Zonulin will be measured on days 0, 5, and 10. The SOFA, APACHE II, and mNUTRIC scores will also be assessed. Mortality will be calculated at 30 and 60 days after the intervention. The secondary outcomes will be SOFA score and 30- and 60-day mortality.

**Discussion:**

Our study aims to present new evidence about the role of protein in enteral nutrition on intestinal permeability in critically ill patients in the ICU.

**Trial registrations:**

The clinical trial was registered on December 11, 2024 in the Iranian Registry of Clinical Trials (IRCT) (IRCT20241129063891N1).

## Background

1

Intestinal permeability is the ability of molecules such as bacteria, toxins, or partially digested food particles to pass through the intestinal epithelium and enter the bloodstream [1]. The intestinal barrier normally includes epithelial cells connected by tight junctions. This setup allows selective nutrient absorption and keeps harmful agents out [2]. However, in serious conditions such as sepsis, severe burns, or major trauma, this barrier can become disrupted. This leads to increased intestinal permeability, often called “leaky gut” [3] (see Fig. 1).

**Fig. 1 fig1:**
[figure not shown]
Leaky gut.

Zonulin is a membrane protein made by intestinal epithelial cells. It affects the permeability of tight junctions, which in turn impacts intestinal barrier function [4,5]. Various triggers, such as certain dietary components such as gluten, harmful bacteria, and inflammatory signals, can cause its release. Increased zonulin secretion leads to the destruction of tight junctions, resulting in increased paracellular transport [6]. When zonulin is excessively elevated or chronically elevated, it may contribute to sustained barrier dysfunction and pathological intestinal permeability [7].

The integrity of the intestinal barrier is vital for patients in the intensive care unit (ICU), as its disruption can lead to severe complications [8]. Increased intestinal permeability in these patients facilitates bacterial translocation and endotoxemia, which are related to systemic inflammatory response syndrome (SIRS), sepsis, and multiple organ dysfunction syndrome (MODS) [9]. These complications significantly contribute to increased hospital stay and mortality rates [9,10]. Enteral nutrition (EN), especially protein intake in ICU admission patients, can reduce associated risks and support patient recovery [11].

EN not only serves as a source of essential macro- and micronutrients but also contributes to the preservation of gut barrier function, the modulation of the immune response, and the reduction of inflammation [12]. The protein content and various amino acids in enteral nutrition for ICU patients have been shown to suppress excessive zonulin release, thereby stabilizing tight junctions and reducing intestinal permeability [13]. One study revealed that intestinal permeability damage improved with protein intake during severe heat stress [14]. The consumption of whey protein and glutamine significantly improved intestinal permeability and intestinal morphology in patients with Crohn's disease [15]. Furthermore, the protein component of enteral formulas plays a critical role in intestinal health [16]. In addition to supporting metabolic demands and tissue repair, dietary proteins promote epithelial cell regeneration, tight junction maintenance, mucosal immune defense, and protection against oxidative stress [17]. In ICU patients, who are highly susceptible to gut barrier breakdown and microbial translocation, adequate protein provision is of particular importance for improving clinical outcomes [18]. According to the ESPEN guidelines [19], critically ill patients must be supplied with approximately 1.3 g/kg/day protein. Similarly, the ASPEN guidelines [20] recommend 1.2–2.0 g/kg/day based on disease severity, metabolic stress, and nutritional status. In cases such as severe burns or major trauma, the requirements may increase to 2.5 g/kg/day.

Essential nutrients are vital for maintaining intestinal barrier function. A lack of protein can lead to villous atrophy, reduced expression of tight junction proteins, increased bacterial movement, and increased intestinal permeability. Some studies have shown a significant relationship between intestinal permeability, nutritional support, and protein intake in certain patients. Zonulin, a physiologic controller of intercellular tight junctions, is crucial for protecting against microorganisms in the intestine and is involved in intestinal immunity. An elevated level of zonulin has been reported in septic ICU patients [21]. We hypothesize that protein intake might reduce intestinal permeability and lower circulating zonulin levels in critically ill patients. Studies in critically ill patients are limited. Consequently, our study aimed to investigate the effects of high-protein (HP) versus conventional-protein (CP) intake in enteral nutrition on intestinal permeability, disease severity, and mortality in critically ill patients in the ICU.

## Methods/design

2

### Trial design

2.1

This study is a randomized, double-blind clinical trial with two groups that receive different doses of protein via enteral nutrition: the CP group and the HP group. All patients will received enteral nutrition through tube feeding. Critically ill patients admitted to the ICU will be eligible for enrollment 24 h after admission. Protein administration begins 48 to 72 h after admission, depending on the patients' suitability. The acute physiology and chronic health evaluation II (APACHE II) and modified nutritional risk in critically ill (mNUTRIC) scores will be assessed at ICU admission. Sequential Organ Failure Assessment (SOFA) score will be evaluated at the beginning and end of the intervention period. Blood samples will be collected on days 0, 5, and 10 for the measurement of zonulin levels and intestinal permeability. Serum zonulin has been widely used in clinical studies as a practical and minimally invasive biomarker reflecting intestinal barrier function [22]. Established tests for intestinal permeability, such as the lactulose/mannitol ratio, are limited in critically ill ICU patients due to practical and clinical constraints, including the need for enteral substrate administration, timed urine collection, and potential hemodynamic instability [23]. Therefore, we used serum Zonulin as a reliable biomarker for intestinal barrier function in ICU patients. [13,21,22,24]. The medication administered during the intervention will be documented and organized by drug class. During the 10-day intervention, patients will be under continuous clinical observation and full monitoring by the treatment team and will be constantly monitored for protein feeding tolerance. The blood samples will be centrifuged and frozen at −70 °C until laboratory analysis. Finally, data on zonulin levels, intestinal permeability, and clinical scores will be analyzed via SPSS and appropriate statistical methods. The trial procedure is illustrated in the flow chart presented in Fig. 2. The protocol was created following the SPIRIT guidelines (see Table 1).

**Fig. 2 fig2:**
[figure not shown]
The flowchart of the study protocol.

**Table 1 tbl1:**
[figure not shown]
The SPIRIT includes a checklist of enrollment, interventions, and assessments.

### Study setting

2.2

The clinical trial will be conducted at the ICU of Hazrat Rasool Akram Hospital in Tehran under the joint academic supervision of Mashhad University of Medical Sciences and Iran University of Medical Sciences. Both institutions collaborate in the oversight of study implementation, adherence to ethical standards, and data quality assurance. The study subjects will be critically ill patients admitted to the ICU 24 h after admission. The participants will be selected via a simple random sampling method. Eligible patients will be between 18 and 65 years old and categorized under general ICU admission.

A total of 88 critically ill patients who fulfill all the inclusion and exclusion criteria will be recruited on the basis of previous studies and sample size calculations. The principal investigator ([name]) After providing informed consent from the patient's legal guardian—following a full explanation of the study's objectives and procedures, emphasizing confidentiality and voluntary participation—patients will be randomly allocated to either the control or intervention group, with 44 patients in each. Recruitment procedures will involve in-person visits to the ICU by the research team. Throughout the study period, all participants will be monitored under the supervision of a board-certified intensive care specialist ([name]).

### Eligibility criteria

2.3

Individuals will be screened for eligibility, and informed consent will be obtained.

### Inclusion criteria

2.4

The criteria listed below are required for participation and enrollment in the study.•Age between 18 and 65 years (inclusive), of either sex•ICU admission for at least 24 h•Initiation of EN for a minimum of 24 h prior to enrollment•Hemodynamically stable at the time of inclusion•Receiving ≥60% of the prescribed protein requirements via EN (for various reasons, such as severe catabolism, adequate protein intake cannot be achieved via EN alone after 3-7 days, and approximately 60% of the total protein requirement is provided enterally, it is advisable to initiate supplemental parenteral nutrition (SPN) alongside enteral nutrition to provide protein and calorie intake to patients).•Provision of written informed consent by the patient's legal representative following full disclosure of the study objectives and procedures.

### Exclusion criteria

2.5

Participants will be excluded from the study if any of the following conditions are met.•Diagnosis of sepsis at the time of screening•Presence of chronic conditions such as liver cirrhosis, stage 3 or 4 chronic kidney disease, or acute renal failure (ARF)•Diagnosis of malignancy with receipt of chemotherapy within the past month•Known gastrointestinal disorders, including celiac disease, Crohn's disease, ulcerative colitis, or short bowel syndrome•Use of immunosuppressive agents (e.g., corticosteroids) within one week prior to enrollment•Use of probiotic supplements within one month prior to enrollment•Pregnancy or lactation•Body mass index (BMI) <18 or >40 kg/m^2^

### Reasons for eliminating the data

2.6

•Expected ICU stay of less than 48 h•Patient death or discharge before day 4 of the study•Use of glutamine supplement during the study period•NPO (nil per os) status for more than 4 consecutive days•Presence of any absolute contraindication to EN•Refusal or withdrawal of consent at any stage of the intervention

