#### Enteral protein administration

2.10.8

Gavages will be administered by personnel blinded to the baseline assessments. Once each patient's hemodynamic status is stabilized, tube feeding (via a nasogastric tube or gastrostomy) is initiated. High-protein feeding begins 48 h after ICU admission and continues until either ICU discharge or day 10 of the study. Enteral feeding will be given intermittently every 3 h. The feeding volume will be determined on the basis of each patient's caloric requirements and tolerance. During the first 24 h, 30% of the total caloric need will be initiated. If well tolerated, the volume was gradually increased to the target level. The protein and energy goals should be increased gradually and achieved within the first 48 to 72 h to avoid overfeeding.

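### Expected ICU stay is listed as a reason to eliminate data, not as an entry criterion, and its 48 h horizon has no stated clock and does not fit the trial's calendar

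*Protocol article*

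**What the plan says.** All references are to the protocol article.

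- **Entry.** Section 2.2 recruits patients who meet the inclusion and exclusion criteria. The only ICU-stay item in 2.4 looks backward: "ICU admission for at least 24 h". Section 2.5 has no stay item.
- **Elimination.** Under the heading "Reasons for eliminating the data", section 2.6 lists "Expected ICU stay of less than 48 h" and "Patient death or discharge before day 4 of the study", alongside events that can only happen during the study, such as glutamine use and withdrawal of consent. It does not say when the expected stay is judged or from what moment the 48 h runs.
- **Start of study protein.** Section 2.1: "Protein administration begins 48 to 72 h after admission, depending on the patients' suitability". Section 2.10.8: "High-protein feeding begins 48 h after ICU admission and continues until either ICU discharge or day 10 of the study". The same section says that the protein and energy goals "should be increased gradually and achieved within the first 48 to 72 h".
- **Measurement.** Zonulin is sampled on days 0, 5 and 10 (2.1 and 2.10.11).
- **Allowance for loss.** Section 2.9 raises 41 per group to 44 for 5% attrition.

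**The concern.** An expected stay is a forecast, and a forecast is a baseline judgement. Used before allocation, it only defines the population and cannot bias the comparison. Used after allocation, it takes randomised patients out of the data, and the person applying it may already have seen how the patient is doing. The protocol places it in the second role.

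The chosen horizon adds to the problem. The question is what 10 days at two protein levels do to zonulin. A patient who just clears 48 h may leave the ICU before study protein has started, or within a day of its start, and before any follow-up sample. At stake are randomised patients lost for a reason that could have been settled at screening, a small attrition allowance, and a comparison that also has mortality and length of stay as secondary outcomes (2.10.5).

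**Working it through.** **1. Is there an entry rule on expected stay?** In 2.4 the stay item concerns time already spent in the ICU. In 2.5 there is none. The only forward-looking rule is in 2.6. So even a patient expected to stay less than 48 h meets the entry lists, can be randomised, and then qualifies for removal.

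**2. Study protein received by a patient who just passes the 48 h rule.** Inputs: threshold 48 h (2.6); earliest enrolment 24 h after admission (2.1); study protein from 48 h (2.10.8) or up to 72 h (2.1); planned duration 10 days, or 240 h (2.10.3); study protein ends at ICU discharge or day 10 (2.10.8).

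Hours received = max(0, time of ICU discharge after admission − time of study-protein start).

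| Clock for the 48 h | Discharge after admission | Start at 48 h | Start at 72 h |
|---|---|---|---|
| Admission | 48 h | 0 h | 0 h |
| Enrolment at 24 h | 24 + 48 = 72 h | 24 h (24/240 = 10%) | 0 h |
| Enrolment at 48 h | 48 + 48 = 96 h | 48 h (20%) | 24 h (10%) |

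Counted from admission, the threshold is no longer than the wait for study protein. Counted from enrolment at 24 h, the wait is 24 to 48 h, and the threshold equals only its upper end. The answer therefore depends on a clock that the protocol does not state.

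**3. What the day-4 rule does with that patient.** If day 0 is enrolment at 24 h, day 4 falls at 24 + 96 = 120 h after admission. Discharge at 48, 72 or 96 h is earlier, so the patient is eliminated (reading discharge as ICU discharge, which 2.6 does not specify). A patient who remains until day 4 has had at least 120 − 72 = 48 h to 120 − 48 = 72 h of study protein. If day 0 is instead the start of study protein, that minimum is 96 h.

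**4. What the day-4 rule leaves open.** A patient discharged on day 4 itself passes both rules, but study protein stops at ICU discharge and the next sample is on day 5. The article describes no sampling after discharge.

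**5. Allowance.** The plan's own figure reproduces: 41 / 0.95 = 43.2, rounded up to 44. The margin is 44 − 41 = 3 per arm, or 3/44 = 6.8%, and it has to cover every reason in 2.6. The share of short-stay patients is not in the documents. As an assumption only: 5% gives 2.2 per arm, 10% gives 4.4 and 20% gives 8.8. The 41 is taken here as stated.

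**The case against.** **The item may simply be misfiled.** Section 2.6 does not say when expected stay is judged. This item, like the one on absolute contraindications to EN, reads like a screening condition printed under the wrong heading. That may be the intention, and removal after allocation is an inference from the placement. It is nonetheless what the text provides for, and a condensed article that prints both eligibility lists should have the item in one of them.

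**Other criteria already favour longer stayers.** Section 2.4 requires at least 24 h of enteral feeding before enrolment, haemodynamic stability and at least 60% of prescribed protein by the enteral route. Enrolment exactly at 24 h would need feeding from the moment of admission. This stands: the 0 to 24 h figure rests on the earliest possible enrolment, and enrolment at 48 h with the clock from there gives 24 to 48 h. These criteria make short stays less likely but do not set an expected duration.

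**Blinding limits the bias.** Section 2.8 blinds clinical staff and outcome raters, so a removal need not follow the arm. That helps, but the section itself concedes that complete blinding may be hard, and the patient's course can itself depend on the arm.

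**Stronger readings that the documents do not support.**
- That the 48 h threshold is what lets short-stay patients in. A rule that does not screen admits nobody by its length; they enter because no criterion covers expected stay.
- That such patients dilute the analysed contrast by 10 to 20%. The day-4 rule removes most of them, and no such share is given.
- That they go unfed. Enteral feeding is already running at enrolment; it is study protein that may not have started.
- That the goals take 48 to 72 h beyond the start of study protein. The text does not say from when that interval is counted.

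**Conclusion.** The point holds as a misplaced and ill-fitting rule. Expected stay is absent from 2.4 and 2.5 and appears only in 2.6, without a clock, so the plan as written permits randomising patients and then removing them on a prognosis knowable at baseline. A patient who just passes would receive 0 h of study protein with the clock at admission, or 0 to 24 h with the clock at enrolment at 24 h, and would then fall under the day-4 rule.

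The main harm is avoidable removal after randomisation, open to influence from the patient's course and charged to an allowance of 3 per arm. Dilution is secondary. How many patients are affected cannot be derived from the documents; the allowance is exceeded once removals for all reasons pass 3 of 44 per arm. The conclusion does not rest on any assumed share of short stayers, but the exposure figures do rest on the unstated clock, the earliest enrolment time and the meaning of day 0.

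**What to change.** Before recruitment starts:

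- Move the expected-stay rule from 2.6 to 2.5 as an exclusion, judged and recorded before the allocation envelope is opened, and delete it from 2.6.
- State the moment from which the expected stay is counted, and define day 0.
- Reconcile the horizon of the rule with the start of study protein, which 2.1 and 2.10.8 give differently, and with the day-5 zonulin sample, so that 2.1, 2.4, 2.6 and 2.10.8 describe one calendar.

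The cost is one eligibility amendment; the Trial registration section says that recruitment has not begun. Relocating the rule costs almost nothing. A longer horizon would slow enrolment slightly and limit the population somewhat to longer-stay patients, which the report should then say. The day-4 rule still removes randomised patients on death or discharge, and moving the expected-stay rule does not settle that.

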### Sample size

2.9

The sample size was determined on the basis of serum zonulin levels, which were considered the primary outcome of the study. In the study by Klaus et al. [21], the mean zonulin level in the target patient population was reported to be 3.40 ng/mL, with a standard deviation of 0.71. A type I error (α) of 0.05 and a statistical power (1−β) of 80% were used for the calculation. A 10% change in zonulin levels was deemed clinically significant. This threshold was chosen based on previous reports of variation in zonulin levels in critical illness and feasibility considerations for sample size estimation [21]. The exploratory nature of this outcome is acknowledged. Using the standard formula for sample size estimation based on a two-sided independent samples *t*-test to determine the mean of the intervention group versus the control group, the required sample size was calculated to be 41 participants per group, or a total of 82 participants. The final sample size was adjusted to 44 participants in each group, out of a total of 88 participants, considering an expected attrition rate of 5% during the study period.

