#### Secondary outcomes

2.10.5

•SOFA questionnaire•30-day and 60-day mortality rates•Length of stay (LOS) in a hospital

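### Section 2.6 deletes randomised patients for events after allocation, including early death, which removes outcome events and can bias the comparison between arms

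*Protocol article*

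**What the plan says.** The protocol article lists inclusion criteria in section 2.4 and exclusion criteria in 2.5. A separate section, 2.6, is headed "Reasons for eliminating the data". Its six items differ in timing.

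- Clearly during the study: "Patient death or discharge before day 4 of the study"; "Use of glutamine supplement during the study period"; "NPO (nil per os) status for more than 4 consecutive days"; and "Refusal or withdrawal of consent at any stage of the intervention" (withdrawal, although a refusal could come before allocation).
- Could be settled at screening: "Expected ICU stay of less than 48 h", and the presence of an absolute contraindication to enteral nutrition (EN).

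Section 2.2 allocates patients after consent, 44 to each arm. Sections 2.1 and 2.10.8 place sampling on days 0, 5 and 10 and run the feeding to ICU discharge or study day 10. Section 2.10.5 names "30-day and 60-day mortality rates", SOFA and hospital length of stay (LOS) as secondary outcomes. Section 2.10.16 plans Kaplan-Meier and Cox analyses for time-to-event outcomes. The only allowance for losses is in section 2.9, where the sample size is raised "considering an expected attrition rate of 5% during the study period".

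The article does not limit section 2.6 to the zonulin analysis, does not keep eliminated patients for mortality or LOS, and does not state that patients are analysed as randomised.

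**The concern.** Randomisation makes the two groups of 44 comparable at allocation. A rule that then drops patients because of what happened to them replaces those groups with groups selected on later events, some of which may depend on the protein dose. The article itself treats tolerance of protein as something to be managed (divided doses in 2.10.7, tolerance monitoring in 2.1), and prolonged fasting can follow intolerance.

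For two outcomes the problem is more direct. A death before day 4 is an event of the mortality endpoint, and the rule deletes it. A discharge before day 4 is among the shortest stays, and the rule deletes that too. Both values are known for these patients, so the data are discarded rather than missing.

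At stake is the mortality comparison. An arm with more early deaths would look better than it is. On LOS the effect can run the other way: an arm with more early recoveries would lose its best results.

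**Working it through.** **The plan's own figure.** Section 2.9 goes from 41 to 44 per arm for 5% attrition: 41/0.95 = 43.2, rounded up to 44. That step reproduces. It allows for 44 − 41 = 3 losses per arm, and it addresses numbers only. No inflation of the sample corrects for selective loss.

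**Is day 4 after allocation?** Allocation follows consent (2.2), day 0 is the sample before the intervention (2.10.11), and the study-day count runs to day 10 (2.10.8). Day 4 therefore lies within the intervention and after randomisation.

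**Effect on mortality.** Let N = 44 be randomised per arm (2.2), D the deaths by the mortality time point, and E those before day 4. The documents give neither D nor E, so every count below is an assumption.

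- All randomised: D/N
- After eliminating early deaths: (D − E)/(N − E)

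HP is the high-protein arm and CP the conventional-protein arm; differences are HP minus CP.

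| Assumed case | All randomised, HP vs CP | After elimination, HP vs CP |
|---|---|---|
| A: D = 12 and 12; E = 4 (HP), 1 (CP) | 12/44 = 27.3% vs 12/44 = 27.3%; difference 0 | 8/40 = 20.0% vs 11/43 = 25.6%; difference −5.6 points |
| B: D = 15 (HP), 11 (CP); E = 6, 2 | 34.1% vs 25.0%; difference +9.1 points | 9/38 = 23.7% vs 9/42 = 21.4%; difference +2.3 points |
| C: D = 13 and 13; E = 4 and 4 | 29.5% vs 29.5%; difference 0 | 9/40 = 22.5% in both; difference 0 |

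Case A creates a benefit from nothing, case B hides most of a harm, and case C leaves the contrast intact but lowers both rates by 7 points.

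Removing early deaths alone always lowers the absolute rate when E > 0 and D < N. The same item also removes early discharges. If S of these are survivors, the analysed rate is (D − E)/(N − E − S), which is below D/N only when E(N − D) > D·S. With D = 12 and E = 4 this is 128 > 12·S, so the rate is understated for S up to 10.

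**Effect on zonulin.** Take no true difference, the SD of 0.71 from section 2.9, and an assumed correlation of 0.5 between the tendency to be eliminated and zonulin. With a proportion p eliminated, the mean of those kept falls by 0.5 × 0.71 × φ(c)/(1 − p), where c is the standard normal quantile at 1 − p.

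- p = 10% in both arms: no shift between arms.
- p = 5% (CP) and 15% (HP): −0.355 × (0.274 − 0.109) ≈ −0.06 ng/mL.
- p = 5% (CP) and 25% (HP): −0.355 × (0.424 − 0.109) ≈ −0.11 ng/mL.

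The planned difference is 10% of 3.40 = 0.34 ng/mL, so these shifts are about 17% and 33% of it. The correlation and the proportions are assumptions.

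**The case against.** Several points on the other side are fair.

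- **Not every item is post-allocation.** Expected stay and an existing contraindication to EN can be checked at screening. A reader might infer that all six items break the randomisation, or that the rule concerns contraindications that develop later. The text speaks of presence, so it does not support that. Four items remain.
- **Bias is possible, not shown.** A reader might infer that the rule does bias all four outcomes. The documents give no rates by arm, and case C shows that equal early deaths leave the mortality contrast unchanged. In case A, early deaths of 4 and 1 out of 44 are compatible with chance (Fisher p about 0.36). The example shows what the rule can do, not what it will do here.
- **Blinding and gradual feeding.** Staff are to be blinded (2.8), and protein is built up over 48 to 72 hours (2.10.8), so the arms may differ little before day 4. This makes strongly differential early loss less likely but does not exclude it. It does not cover fasting, glutamine use or withdrawal, which can occur later in the intervention. Blinding also does not prevent selection on a true effect of the feed.
- **Some data cannot be recovered.** A patient who dies before day 4 has no day 5 or day 10 zonulin and no SOFA score at day 10, whatever the rule. For those outcomes, retaining the patient is not enough.
- **Analysis sets are often left to an analysis plan.** That would answer a complaint about silence. Here the article states a rule, and a later plan that analysed everyone would contradict it.

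A reader might also infer that the eliminations explain low power for zonulin. That does not belong here. Whether 41 per group follows from the stated inputs is a separate question, and losses between days 4 and 10 are mostly not deletions under section 2.6.

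**Conclusion.** The concern holds in this form. As written, section 2.6 removes early deaths from the mortality endpoint and early discharges from LOS. Its deletion of early deaths, taken alone, understates absolute mortality. It can bias the contrast between arms for mortality, LOS, SOFA and zonulin if the eliminated patients differ by arm.

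The conclusion that outcome events are dropped rests only on the text. The size does not: the 5.6-point false difference in case A, the other mortality cases and the zonulin shifts all depend on assumed inputs, and the documents do not establish a direction. The point should be settled before recruitment because the rule is explicit and bears on the trial's own secondary outcomes.

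**What to change.** Replace section 2.6 with a statement that all randomised patients are analysed in the group to which they were assigned. Specifically:

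- Mortality (Kaplan-Meier and Cox, timed from randomisation) and LOS use every randomised patient. The Mortality section counts 30 and 60 days after the intervention; timing from randomisation makes clear that deaths during the feeding period count.
- Zonulin and SOFA use all available measurements, with a stated handling of death. Worst-rank scoring or SOFA 24 for deaths, and days alive and out of hospital in place of LOS, are options rather than requirements.
- The post-allocation rules (early death or discharge, glutamine, fasting, withdrawal) apply only in a labelled per-protocol sensitivity analysis.
- Data collected before withdrawal are kept unless deletion is requested.
- The text makes clear that expected ICU stay and absolute contraindication to EN are screening conditions applied before randomisation.
- Patients who meet a post-allocation rule are reported by arm and reason.

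The cost is protocol wording. Vital status is already to be obtained from hospital records or by telephone (Mortality section), and recruitment had not started when the article was finalised. The downside is some dilution of the effect by patients who received little of the study feed; the per-protocol sensitivity analysis would show how results look without them.
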